### Patient recruitment strategy

2.6

For recruitment purposes, physicians and SNPs will be asked to identify patients with a diagnosis of CMD for whom a decision of sick leave has been made or may be considered. These patients will be referred to the occupational therapist. If they agree to participate in the study, a member of the research team will meet them to verify their eligibility, and to obtain their informed consent to participate in the study. Recruitment will take place over 12 months in each U-FMG.

To be eligible patients must be: 1) consulting a family physician or a SNP for a CMD, 2) referred to the occupational therapist for a new episode of sick leave or wish to prevent a sick leave, and 3) able to speak, read, and understand French or English. In this study, CMDs include depressive disorders, anxiety disorders, obsessive-compulsive disorder, and trauma- or stress-related disorders, including adjustment disorders (49). Patients will not be eligible if they: 1) have a diagnosis of a severe mental disorder limiting work integration or participation and 2) require or receive services from a specialized mental health care team.

### Data collection

2.7

#### U-FMG and participants' characteristics

2.7.1

##### Case study characteristics

2.7.1.1

To provide a rich description of the study context, the following information on each U-FMG will be collected: number of registered patients, physicians, other professionals, and available resources (e.g., electronic medical record). Managers of the U-FMG will be consulted and local data will be used to collect this information. Qualitative data on the characteristics of the U-FMG's will also be collected in a focus group using a semi-structured interview guide based on the CFIR domains and constructs.

##### Patients' sociodemographic characteristics and RTW related factors

2.7.1.2

Data will also be collected to describe the patients who received the occupational therapy program. An online questionnaire will be administered at the time of recruitment to document the following patient characteristics: gender, sex, age, race/ethnicity, education level, marital status, employment status, type of employment, household income, diagnosis, number of previous sick leave episodes and their duration, reasons for sick leave, type of insurance coverage, number of days absent from work, number of hours worked per week if partial sick leave, type and sector of employment, and company size. Source of referral (either the family physician or the SNP) will also be documented, whether the patient is or not registered with this professional, and since when.

#### Characteristics of health care and social services received by patients

2.7.2

##### Description of the occupational therapy interventions received

2.7.2.1

To document how occupational therapy interventions are implemented in the three U-FMGs, each occupational therapist will fill out a logbook for each patient describing frequency, duration, types, and modality of the interventions provided. Furthermore, information on stakeholders’ involvement, and on collaboration with other U-FMG team members, external professionals, and stakeholders will also be collected.

##### Description of other health and social services used by patients

2.7.2.2

We will also document information on other health and social services accessed and used by the patient (e.g., psychologist, Employee and Family Assistance Program, private occupational therapy, etc.) via a self-administered questionnaire completed at the end of the study to evaluate the possible influence of accessing those resources.

#### Assessing the acceptability of the occupational therapy program (objective 1)

2.7.3

Acceptability of the intervention will be assessed in three phases: pre-implementation, during implementation, and post-implementation (**Table 3**).

**Table 3 T3:** Accessibility assessment data collection according to study frameworks and implementation phase.

Data collection methods	TFA	CFIR	Pre-implementation	During implementation	Post-implementation
TFA questionnaire *	X		X		X
Focus Groups**	X	X	X		X
Minutes from implementation support committee meetings**	X	X		X	
Research coordinator and occupational therapist logbook**	X	X		X	
Emails between research team and implementation support committee **	X	X		X	
Semi-structured interview with occupational therapists**	X	X			X
Semi-structured interview with patients**	X				X

*Quantitative data collection; **Qualitative data collection.

##### Pre-implementation acceptability

2.7.3.1

Two strategies will be used to document pre-implementation acceptability: TFA questionnaire and a focus group in each participating U-FMG.

The TFA questionnaire will be completed by U-FMG team members, occupational therapists, and patients at the time of recruitment. It is an 8-item generic questionnaire assessing the seven components of acceptability. It can be adapted for any intervention (50). Each item is scored on a five-level Likert scale which allows to produce a score from 8 to 40, 40 being the highest level of acceptability. It was developed using participatory methods and is based on Sekhon et al. (36) theoretical framework. For the purpose of our study, it will be adapted to the context of the occupational therapy program with the support of our research team, which includes our patient partners, a family physician and occupational therapists. It will also be translated into French using online translation tools and validated through the consultation of our research team. Pretest of the questionnaire will be conducted with five patients, healthcare professionals and occupational therapists not participating in the study to ensure clarity of items.

The pre-implementation focus group will be conducted in each U-FMG to understand team members’ expectations related to the implementation of the program. The focus groups will involve 9 participants, including physicians and SNPs (n=4), U-FMG managers (n=3), a nurse (n=l), and a social worker (n=1). An interview guide based, on the TFA model by Sekhon et al. (36), will be used to document expectations, needs, readiness to change, perceived sense of control, and contextual elements that could facilitate or hinder the implementation of the intervention according to each of the model's domains. The group will be facilitated by a member of the research team and a patient partner. This data will be used to adapt the occupational therapy program according to the characteristics of the U-FMG context (e.g., team functioning, modes of communication, sharing of roles between team members).

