##### Occupational Balance Questionnaire

2.7.4.5

The Occupational Balance Questionnaire will be used to document the person’s level of life balance, i.e., the extent to which a person achieves a good quantity and variation of occupations. The score of this questionnaire is strongly correlated with perceived health (63, 64). The original version demonstrates a good internal consistency, and satisfactory test-retest reliability (63). The French-language version of this questionnaire demonstrated good internal consistency and satisfactory test-retest reliability in Quebec (64).

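### No described step checks that the French TFA questionnaire, the only quantitative acceptability measure, keeps the meaning of its items

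*Protocol article*

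**What the plan says.** The protocol article, section 2.7.3.1, describes the TFA questionnaire: "It is an 8-item generic questionnaire assessing the seven components of acceptability". On scoring: "Each item is scored on a five-level Likert scale which allows to produce a score from 8 to 40".

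Three preparatory steps are then stated:

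- **Adaptation.** The article says that "it will be adapted to the context of the occupational therapy program with the support of our research team". That team is said to include patient partners, a family physician and occupational therapists.
- **Translation.** "It will also be translated into French using online translation tools and validated through the consultation of our research team".
- **Pretest.** "Pretest of the questionnaire will be conducted with five patients, healthcare professionals and occupational therapists not participating in the study to ensure clarity of items". No language is given for the pretest.

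Table 3 (section 2.7.3) marks the TFA questionnaire as the one quantitative source for acceptability. The other six sources are qualitative. Patients are eligible if they are "able to speak, read, and understand French or English" (section 2.6).

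Section 2.8.1 uses the questionnaire in four ways: descriptive statistics, a paired pre/post test, a joint display with the qualitative findings for each TFA component, and a cross-case comparison of results matrices.

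**The concern.** The article states a method here, and the method is weak for what is asked of it. Machine translation followed by consultation within the team can produce fluent French items that no longer ask the same question. Burden, opportunity costs and ethicality are abstract ideas, and such items can read clearly and still be off target. A pretest for clarity would not catch that.

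The article reports more for some other instruments. For the Occupational Balance Questionnaire, section 2.7.4.5 says: "The French-language version of this questionnaire demonstrated good internal consistency and satisfactory test-retest reliability in Quebec". For the Work Role Functioning Questionnaire, section 2.7.4.9 cites validity and internal consistency of a Canadian French version. The TFA items are both adapted and translated for this study, so published evidence on the generic form does not carry over automatically.

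At stake is the quantitative half of objective 1, mainly the component-level joint display and any comparison of score levels between people who answered in different languages. If nearly everyone answers in French, the language comparison matters little. The French text is then in effect the instrument, and its content matters all the more.

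**Working it through.** **Inputs.** Eight items, seven components, five response levels, total 8 to 40 (section 2.7.3.1). French or English patients (section 2.6). Paired test, joint display and cross-case comparison (section 2.8.1). The article gives no standard deviation, target difference, language mix or sample size for the TFA score.

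**1. The stated range.** Assuming items are scored 1 to 5, the minimum is 8 × 1 = 8 and the maximum is 8 × 5 = 40. This reproduces the article's range. Translation leaves it unchanged and can only alter what a given score means.

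**2. Items per component.** If each of the seven components has at least one item, 8 − 7 = 1 item is left over. At most one component can then have two items, so at least 7 − 1 = 6 components rest on a single item.

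**3. What one misread item does (illustration only; the one-point shift is assumed).**

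| Level | Width of scale | Shift | Share of width |
|---|---|---|---|
| Total score | 40 − 8 = 32 | 1 | 1/32 ≈ 3% |
| Component with one item | 5 − 1 = 4 | 1 | 1/4 = 25% |

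The total dilutes the error. A single-item component does not, and the joint display works component by component.

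**4. The paired test.** Let a French version add a constant *b* to a person's score. With the same version at both times, the change is (post + *b*) − (pre + *b*) = post − pre, so *b* cancels. With a change of version between times, the change is off by +*b* or −*b*. The article does not say which version a person receives at each time. Cancellation also covers only a constant shift. If an item asks about something else, the change score tracks that something else.

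**5. Score levels between groups.** If the French shares in two groups are *p*₁ and *p*₂, the difference in means is off by *b* × (*p*₁ − *p*₂). It is 0 when the shares are equal and reaches *b* in absolute size when one group is all French and the other all English. The article gives neither *b* nor the shares, so only this range from 0 to *b* can be stated.

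**6. The checks described.** Team consultation can catch awkward or obviously wrong wording. The outside pretest can catch items that people do not understand. Neither is described as comparing the meaning of the French item with its source.

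**The case against.** The other side has several fair points.

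- **The team is not the only check.** The pretest uses people outside the study. This stands, and it would be wrong to say that only the study's own team looks at the wording. The pretest's stated purpose is still clarity.
- **The paired test is largely protected.** This stands for a constant shift with the same version at both times. A reader might infer that the pre/post result itself is biased. The document does not support that as a general statement.
- **Between-group harm is indirect.** Section 2.8.1 plans no statistical test of TFA totals between clinics or languages, and the comparison between clinics in section 2.8.2 concerns objective 2. The language criterion is for patients only, and nothing says that the mix differs by site. Pooling of the two languages is an inference from the absence of any mention of a split.
- **Qualitative data may expose a bad item.** They may, because the joint display sets both strands side by side. A mistranslated item could equally appear there as a real disagreement, or a false agreement, between strands.
- **An article condenses.** A back-translation could be described in a fuller protocol. The point therefore rests on what is stated: online tools, and team consultation called validation.
- **The contrast with other instruments is uneven.** For the return-to-work self-efficacy questionnaire, section 2.7.4.8 reports a two-stage French translation, but its measurement properties are cited for the English form. The article does not hold every instrument to the same level of French evidence.

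**Conclusion.** The point holds in a limited form. The stated procedure does not support the word *validated*, and no described step checks that the French items keep their meaning in the only quantitative measure of objective 1. The exposure is greatest in the joint display, where at least six of seven components rest on one item (assuming that every component has at least one). Comparability of French and English score levels is assumed and not shown.

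The size of any bias cannot be estimated from the document. Three stronger readings should be avoided. The 8 to 40 range is not put in doubt by translation. No shift can be called as large as the change the study is looking for, because no target change is given. The text does not say that those who review the wording are the people who developed the program; it says only that they are the study's research team.

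This is an inexpensive improvement worth making before first use. It does not undermine the study: acceptability also draws on six qualitative sources, and no decision threshold is tied to the score.

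**What to change.** In section 2.7.3.1:

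1. Have two bilingual team members independently translate the adapted items, or correct the machine output, and reconcile their versions. Have another bilingual team member who has not seen the source items back-translate the result, and compare it with the source before first use. This assumes that the team has three such members; the article does not say.
2. Run the planned pretest in the languages to be used, and ask respondents to say in their own words what each item means, in addition to whether it is clear.
3. Record the language version for every questionnaire and keep it the same for each person at both time points.
4. Report TFA results descriptively by language where numbers allow. Reliability statistics by language are not requested, because English respondents may be too few for them.
5. Replace the word *validated* with *reviewed*.

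The cost is a few days of team time and no additional study participants. The downside is a possible short delay if items need rewording. The work has to come before the first baseline questionnaire, because changing items afterwards would break the pre/post comparison.

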##### Acceptability during implementation

2.7.3.2

At each U-FMG, an implementation support committee will be set up to ensure effective coordination of the implementation and data collection processes. Meetings of the implementation support committee will be recorded, and minutes of each meeting will be produced. Moreover, elements facilitating or hindering the implementation of the occupational therapy program will be documented. The research coordinator will keep a logbook describing the steps taken each week (highlights from emails, phone calls, or meetings). Occupational therapists will also keep a logbook to document their perceptions of challenges or successes in implementing interventions and collaborating with other U-FMG professionals. E-mail exchanges between members of the research team and members of the implementation support committee will also be analyzed to document collaboration.

##### Post-implementation acceptability

2.7.3.3

Three strategies will be used to document post-implementation acceptability: TFA questionnaire, semi-structured interviews, and focus groups.

The TFA questionnaire will be completed a second time, at the end of the implementation phase, by the U-FMG team members and the occupational therapists to compare pre- and post-implementation acceptability results. To document the perspective of physicians and SNPs who would not have referred patients to the occupational therapist, an additional open-ended question will be added to document the reasons associated with these practices. Patients who will have received the occupational therapy program will also complete the TFA questionnaire at the time of discharge in occupational therapy for post-implementation assessment.

Semi-structured interviews will be conducted with ten to 15 participating patients from each of the U-FMGs. A maximum variation purposeful sampling strategy will be used to recruit patients with different characteristics within the sample of subjects who received the intervention (51). We will recruit patients in consideration of their gender, age, level of education, socio-economic level and whether or not they had access to private insurance. Patients who had previously experienced a sick leave related to a CMD will also be recruited to compare their experiences in terms of access to services and perceived effects. The interview guide will be developed based on the TFA model. Semi-structured interviews are expected to last between 30 and 60 minutes and will be conducted via a web conference platform.

Interviews will also be conducted with the participating occupational therapists, using an interview guide based on the TFA model and the CFIR to document the occupational therapists’ perspective on the acceptability of their interventions and the contextual factors that influenced the acceptability of the program. They will also be asked to comment on the future, larger-scale implementation of the program in other U-FMGs or FMGs. Semi-structured interviews will last approximately 60 minutes and will also be conducted via a web conference platform.

We will also conduct a focus group with each of the U-FMG teams. The group will be composed of approximately nine participants, including physicians and SNPs (n=4), U-FMG managers (n=3), a nurse (n=l) and a social worker (n=1). An interview guide also based on the TFA model and CFIR framework will be used. The group will be facilitated by a member of the research team and a patient partner. **Table 3** summarizes the data collection methods planned at each phase for the accessibility assessment.

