### Study objectives

1.1

In this context, the overall aim of this study is to evaluate the acceptability and explore the effects of an occupational therapist-led program, integrated within FMG in the Canadian province of Québec, that is designed to improve the management of CMD-related sick leave and promote service workers’ recovery and sustainable RTW.

We will describe the perspectives of 1) patients receiving the intervention, 2) occupational therapists providing it, and 3) FMG teams collaborating on its delivery on the acceptability of implementing an occupational therapy-led program in FMG. The effect this program has on the recovery and RTW outcomes of people with a CMD will be evaluated.

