### Conceptual frameworks

2.1

Two conceptual frameworks will be used in this study. The first one is the Theoretical Framework of Acceptability (TFA) developed by Sekhon and collaborators (36). This framework defines acceptability in terms of seven components described in **Table 1**. It helps to identify the barriers perceived by patients that can limit the implementation of an intervention in a given context. The TFA describes that acceptability can be assessed at three time points: 1) prospective acceptability, which allows for assessment of anticipated acceptability; 2) concurrent acceptability, which is assessed whilst participating in the intervention; and 3) retrospective acceptability, which is the assessment of experienced acceptability. In the current study, acceptability will therefore be assessed at three times: 1) before the implementation of the intervention (pre-implementation) to identify factors likely to influence implementation and acceptability (*prospective acceptability*); 2) during the intervention, to identify these factors as they arise (*concurrent acceptability*); and 3) after the intervention is implemented (post-implementation), to document the experience patients had of the intervention (*retrospective acceptability*) (36).

**Table 1 T1:** Components of the Theoretical Framework of Acceptability (TFA) (1).

Components	Definitions
Affective Attitudes	Feelings of the person regarding the intervention.
Burden	The amount of effort perceived to be needed to engage in the intervention.
Ethicality	The degree to which the intervention aligns with a person’s value system.
Intervention coherence	The level of understanding of the person regarding the interventions and its functioning.
Opportunity Costs	The degree to which benefits, profits, or values are forfeited to engage in the intervention.
Perceived Effectiveness	The perceived potential of the intervention to meet its goals.
Self-efficacy	The person’s belief in their capability to carry out the actions needed for the intervention.

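### After recruitment, patient acceptability is planned only among program recipients, so early leavers have no assured second measurement on the main objective

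*Protocol article*

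**What the plan says.** Section 1.1 makes acceptability the thing to be evaluated, with effects only explored: "the overall aim of this study is to evaluate the acceptability and explore the effects of an occupational therapist-led program". Patients are the first of the three perspectives named there.

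The patient data on acceptability are as follows.

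- **Recruitment (Section 2.7.3.1):** "The TFA questionnaire will be completed by U-FMG team members, occupational therapists, and patients at the time of recruitment". The score runs from 8 to 40, and higher means more acceptable.
- **During implementation (Section 2.7.3.2 and Table 3):** committee minutes, e-mails, and logbooks kept by the coordinator and the therapists. On the last of these: "Occupational therapists will also keep a logbook to document their perceptions of challenges or successes". No patient questionnaire or patient interview is listed for this phase.
- **After the program (Section 2.7.3.3), questionnaire:** "Patients who will have received the occupational therapy program will also complete the TFA questionnaire at the time of discharge in occupational therapy".
- **After the program (Section 2.7.3.3), interviews:** ten to 15 patients per clinic, sampled for maximum variation so as to "recruit patients with different characteristics within the sample of subjects who received the intervention". The characteristics are given as: "We will recruit patients in consideration of their gender, age, level of education, socio-economic level and whether or not they had access to private insurance". An earlier sick leave for a common mental disorder is a further characteristic.

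Section 2.8.1 compares pre- and post-implementation scores with a paired t-test or a Wilcoxon signed ranks test. Section 2.7.3.3 also adds an open question for physicians and nurse practitioners who did not refer anyone, to learn why.

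**The concern.** Several components in Table 1, such as burden, opportunity costs, perceived effectiveness and self-efficacy, are plausible reasons for a patient to stop attending. Whether a patient is measured the second time may then depend on the quantity being measured. No later analysis can recover experienced acceptability that was never collected, so this is a matter of data collection and not one to leave to an analysis plan.

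The plan applies the right principle to clinicians, by asking non-users for their reasons, but states no counterpart for patients who stop or never start. Section 3.1 acknowledges that acceptability may look high because interested clinics volunteered. It does not mention selection of patients by completion.

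At stake is the reading of the main objective, in a study that Section 4 presents as the first step towards a randomized trial. A favorable patient score that reflects mainly those who stayed could mislead that next step.

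**Working it through.** The plan gives no dropout rate, expected score or sample size on this point, so there is no figure of its own to reproduce. The check has two parts.

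**1. Who has patient-reported acceptability data, followed as written**

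| Patient | TFA at recruitment | Second TFA | Interview | In paired test |
|---|---|---|---|---|
| Received program, discharged | Yes | Yes | Eligible | Yes |
| Started, stopped early | Yes | Not assured; depends on whether stopping counts as discharge | Eligible if counted as a recipient, but not sought | Only if a second score exists |
| Enrolled, never started | Yes | No | Not in the sampling frame | No |

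The focus groups do not fill the gap, since Sections 2.7.3.1 and 2.7.3.3 compose them of clinic team members only.

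**2. Illustration of size (all inputs assumed except the 8 to 40 range)**

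Let d be the share of patients who leave unmeasured, and g the gap between the mean second score of those measured and the mean that leavers would have given. The mean over everyone is (measured mean) − d × g, so the measured mean is too high by d × g.

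| d | g = 4 | g = 8 | g = 12 |
|---|---|---|---|
| 10% | 0.4 | 0.8 | 1.2 |
| 20% | 0.8 | 1.6 | 2.4 |
| 30% | 1.2 | 2.4 | 3.6 |
| 40% | 1.6 | 3.2 | 4.8 |

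For example, with an assumed measured mean of 32, d = 20% and g = 8, the mean over all patients is 32 − 0.20 × 8 = 30.4.

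The planned test concerns change, not the second score alone. If leavers were already lower by b points at recruitment, the error in mean change is d × (g − b). With d = 20%, g = 8 and b = 4 it is 0.20 × (8 − 4) = 0.8 point, against 1.6 points when b = 0. Recruitment scores exist for every enrolled patient, so b can be estimated from the study's own data. The gap g cannot be estimated unless leavers are asked.

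**The case against.** The case on the other side has real substance.

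- **Interviews do not require discharge.** A reader might infer that nobody who stopped can be heard after recruitment. The text does not support that: interviewees need only have received the intervention, so a patient who stopped partway could be chosen. What stands is that nothing in the sampling plan looks for such a patient.
- **Discharge and receipt are undefined.** Closing the file of a patient who stopped might count as discharge, and the full protocol may say so. The gap is therefore one of no assurance, not of proven absence.
- **Concurrent acceptability.** Section 2.1 describes "concurrent acceptability, which is assessed whilst participating in the intervention" and commits to work "during the intervention, to identify these factors as they arise". A reader might infer a broken promise of patient self-report in this phase. The section does not promise that form of data, and it places patients' experience after implementation. Nor are all sources in this phase from staff or researchers: Section 2.2 puts patient partners on the support committees, although the plan does not present them as treated patients.
- **Non-starters have nothing experienced to rate.** This is partly right. Their recruitment score is kept, and what they can add is a reason and a current view.
- **Direction is not proven.** Some patients may stop because they are back at work and satisfied.
- **Stakes are moderate.** No score threshold or go/no-go rule is stated, and the scores are read alongside qualitative findings in a joint display.

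These points limit the claim and its weight. They do not remove the stated restriction of both post-recruitment patient sources to recipients.

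**Conclusion.** The point holds as a selection rule written into Section 2.7.3.3 and carried into the paired comparison of Section 2.8.1. Patients who leave early have no assured post-recruitment acceptability data, and those who never start have none planned. Experienced acceptability is likely, but not certainly, overstated.

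The size is unknown. The range of 0.4 to 2.4 points rests wholly on an assumed 10 to 30% leaving and an assumed gap of 4 to 8 points. It shows how the error scales and is not an estimate. A reader might infer a bias of established size and direction, but the documents support neither. In an exploratory study with no decision threshold, this is a should-fix.

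**What to change.** - In Section 2.7.3.3, offer the second TFA questionnaire to every enrolled patient: at discharge or, for those who stop early or never start, at that point. State what counts as discharge and as having received the program. Report non-starters' answers separately, because they are not experienced acceptability.
- Add having stopped early or never started to the maximum-variation interview criteria, and widen the sampling frame to match. The number of interviews stays the same.
- Extend to these consented patients the open question on reasons already planned for non-referring clinicians.
- Report recruitment TFA scores by completion status next to the paired result, with the number of patients left out of it.

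The cost is slightly more follow-up of non-attenders, using the existing 8-item form. An additional questionnaire early in the program (for example at week 4) or at a fixed time (for example 16 weeks) is optional. Table 2 allows courses of two to 16 weeks and Section 3.1 foresees a waiting list, so a fixed date would catch some patients mid-program and others after they have finished.
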